## Abstract

**Background:**

Maintenance of physical function, mobility, and independent living are important goals for older adults. However, concerns about falling (CaF) play a central role in the vicious cycle of CaF, inflammation, loss of muscle mass, and decreasing physical function ultimately resulting in negative health outcomes. CaF, like other states of chronic stress and anxiety, can be considered as enduring adverse stimuli affecting the stress systems and the inflammatory system. Therefore, the aim of this study is to investigate whether a reduction of CaF leads to a reduction of stress and therefore possibly reduces chronic low-grade inflammation. Understanding the role and directionality of the effects of inflammation on CaF increases our understanding of age-related loss of mobility and physical function.

**Methods:**

In this study, community-dwelling older adults, aged 70 years and older, will be randomly assigned to either a 4-month, multi-component intervention with exercise training and cognitive-behavioral components or to a sham control group with light stretching exercises, cognitive training, and educational health lectures. For the operationalization of specific CaF, the Falls Efficacy Scale—International will be used. Stress and related psychological symptoms will be monitored using established self-reports and by measuring salivary cortisol. Concentrations of C-reactive protein, interleukin 6, interleukin 10, and tumor-necrosis-factor-alpha, as well as gene expression of selected inflammatory transcripts, will be used as surrogate parameters of the inflammatory status at baseline, after the 4-month intervention and 8-month follow-up.

**Discussion:**

This study will be the first to test whether CaF are related with stress system activity or reactivity or with markers of inflammation in the context of a multi-component intervention with exercise training and cognitive-behavioral components addressing CaF. The reduction of specific CaF or general psychological symptoms should reverse alterations in stress systems, and / or slow down low-grade inflammation. Changes in activity, as well as psychological and biological pathways leading from CaF to muscle loss will be measured, to disentangle the individual contribution to sarcopenia, and to provide an additional pathway to break or slow-down the vicious cycle of CaF and sarcopenia.

**Trial registration:**

German Clinical Trials Register (DRKS): DRKS00029171. Registered 22 July 2022.

**Supplementary Information:**

The online version contains supplementary material available at 10.1186/s13063-024-08462-6.

## Administrative information

Note: the numbers in curly brackets in this protocol refer to SPIRIT checklist item numbers. The order of the items has been modified to group similar items (see http://www.equator-network.org/reporting-guidelines/spirit-2013-statement-defining-standard-protocol-items-for-clinical-trials/).

## Introduction

### Background and rationale {6a}

The increasing life expectancy among older populations presents unique challenges in today’s western societies [1]. Maintenance of physical function, mobility, and the possibility to live independently are important for older adults with regard to health and quality of life. However, this goal is counteracted by the age-related loss of physical function as well as a decreased level of strength and muscle mass. Furthermore, the degenerative process could be reinforced if the older person avoids physical activity and exercise, e.g., due to concerns about falling (CaF). The prevalence of CaF was reported between 20 and 85% in older adults. About 10% of community-dwelling older adults experience excessive CaF [2]. CaF has been identified as an independent risk factor for reduced quality of life, increasing fall risks [3–6], and endangering the independence of community-dwelling older adults. The main consequence is a restriction of activities leading to a downward spiral of inactivity, deconditioning, and loss of confidence, thereby contributing to the development of sarcopenia [7–11].

In 2018, Cruz-Jentoft et al. published a new operational definition of sarcopenia in the name of the “European Working Group on Sarcopenia in Older persons” (EWSGOP2) [12]. The operational definition of sarcopenia includes (1) low muscle strength, (2) low muscle quality or quantity, and (3) low physical performance. Sarcopenia is a progressive and generalized skeletal muscle disorder increasing the risk of adverse outcomes including falls, fractures, physical disability, and mortality. Due to the increasing risk of hospitalization, and increased costs during hospital care, sarcopenia also represents an economic burden for health care systems [13]. Prevalence of sarcopenia varies widely due to different cut-off scores and is reported “with regional and age-related variations between, 1–29% in community-dwelling populations, 14–33% in long-term care populations, and 10% in the only acute hospital-care population examined” [14].

Lopez et al. published a recent article on “the Hallmarks of Aging” where the underlying mechanisms as the biochemical and molecular processes that cause aging address twelve mechanisms. One of these is chronic inflammation, which increases with aging (“inflammaging”). Inflammaging is accompanied by elevated levels of circulating inflammatory cytokines and biomarkers, e.g., C-reactive protein (CRP) and interleukin 6 (IL-6). For all-cause mortality in aging human population, elevated IL-6 concentrations serve as predictive biomarkers [15]. Inflammaging may result from multiple causes such as the accumulation of pro-inflammatory tissue damage, which play a role in obesity and type 2 diabetes [16]. Recent evidence has related acute and chronic stress to the inflammatory pathways in the aging process.

A substantial body of research showed that acute, as well as chronic stress, profoundly affects stress systems, including the hypothalamic–pituitary–adrenal (HPA) axis and the sympathetic nervous system (SNS) [17]. Acute stress induces transient increases in stress system activity and widespread effects on target tissues throughout the entire organism [18]. Long-term exposure to adverse psychological conditions, including chronic stress and anxiety, alters basal activity of stress systems [19] and, more importantly, leads to alterations with pathophysiological importance in cells and tissues throughout the organism. Of particular importance in chronic stress is inflammation. Longitudinal studies, for example in family caregivers of chronically ill relatives, have shown that chronic stress is associated with increases in peripheral inflammatory activity [20]. Stress-induced increases in systemic, low-grade inflammation are a strong candidate for linking chronic stress with disease, because the role of inflammation in predicting morbidity and mortality is undisputed [21]. Inflammation has been identified as a key pathophysiological process in cardiovascular disease, cancer, diabetes, and—most importantly—in age-related diseases such as frailty and sarcopenia [22].

As stated above, CaF has demonstrated an impact for development, maintenance, and exacerbation of sarcopenia [23–25]. One barrier in this field are the different constructs and terms related to CaF [26, 27]. At present, there are different terms that refer to the psychological effects of falls, including, e.g., “concerns about falling”, “fear of falling”, “fall-related anxiety”, or “balance confidence” and “falls-efficacy”. Underlying these concepts are related—but distinct—psychological constructs, which have led to considerable complexity and confusion within the literature. The term “fear of falling” is frequently used in the scientific literature. Nevertheless, the recent “World Falls Guidelines” recommend that clinicians use the term “concerns about falling” (CaF), primarily because the older adult panel preferred the term “concern” over “fear” [27].

In a recent qualitative study, Ellmers and colleagues demonstrated that CaF develop in response to one’s perception of their “aging body” and recognition of their vulnerability to suffering severe injuries, rather than the fall itself. Accordingly, individuals with high CaF tend to be primarily concerned about the anticipated long-term consequences of an injurious fall (e.g., loss of independence) [28]. In addition, CaF demonstrated an impact on gait as older adults with high CaF can adopt a more “cautious gait” by reduced velocity, taking shorter steps, widening the base of support, and spending more time in double limb support [29].

In a preliminary study, we found that these CaF are not only leading to decreased physical activity but are also associated with elevated levels of peripheral inflammation (unpublished results). In this analysis, plasma IL-6 was positively related with self-reported CaF, in older women with sarcopenic obesity, who had experienced a fall event in the past. Accordingly, long-term exposure to adverse psychological conditions, including chronic stress and anxiety, has previously been associated to the upregulation of peripheral inflammatory activity. This is consistent with previous findings that chronic low-grade activation of the immune system has been shown to intensify the decay of skeletal muscle [30–32]. Therefore, a vicious, feed-forward cycle of CaF, inflammation, loss of muscle mass, and decreasing physical function is created that ultimately results in negative health outcomes, i.e., falls, dependence, and death. Additionally, exercise training alone might not disturb this cycle because a person with elevated CaF would exhibit an increasing stress level and thus more inflammatory cytokines blunting the anabolic effects of the intervention. Therefore, this study will utilize a multi-component intervention with exercise training and cognitive-behavioral components to oppose muscular decay as well as address CaF in older adults.

To the best of our knowledge, no published study to date has directly tested whether CaF are related with stress system activity or with any marker of inflammation. Understanding the role and directionality of the effects of inflammation on CaF would significantly increase our understanding of the underlying causes of age-related loss of mobility and open up a number of avenues that would increase the efficacy of interventions aimed at increasing mobility and functional health in later life.

### Objectives {7}

The main and overarching objective of the project is to understand the role of the psychobiological stress response, including stress system alterations and inflammation, in the vicious cycle between CaF, declines in mobility, and development of muscle loss and sarcopenia. Therefore, a well-established intervention aimed at reducing CaF and increasing activity will be performed, to test whether a reduction of CaF can break the vicious cycle, and stop the downward spiral towards sarcopenia.

The specific objectives of the study are described in the following:*Objective 1*: To test whether CaF in older adults are positively related with altered stress system activity, specifically overactivity of the sympathetic nervous system (SNS) and hypoactivity of the hypothalamus–pituitary–adrenal (HPA) axis, and higher levels of systemic low-grade inflammation. It will additionally be tested whether general psychological symptoms (stress, anxiety, depression) are similarly or more strongly associated with stress system activity.*Objective 2*: To test whether a well-established CaF-reduction and exercise program reduce CaF will differentially affect stress system activity and reduce or slow down systemic low-grade inflammation. It will additionally be tested if and how general psychological symptoms (stress, anxiety, depression) are affected by the intervention.*Objective 3*: To test for directionality of the brain-to-immune/immune-to-brain feedback system by investigating whether reduced CaF precede reductions in inflammation (or lower rate of increase) or whether reductions in inflammation precede reductions in CaF (or lower rate of increase) (or both). It will additionally be tested whether general psychological symptoms (stress, anxiety, depression) provide an alternative or additional pathway.*Objective 4*: To test whether higher inflammation at baseline is predictive of lower success in the intervention group.*Objective 5*: To test whether systemic and intracellular inflammation at T0 is associated with lower decreases of CaF from T0 to T1 and T0 to T2.

This project has been preregistered before the start of data evaluation; see osf.io/m84hq.

### Trial design {8}

FEARFALL is a randomized controlled prospective trial with a duration of 3 years. Older adults will be randomly allocated into parallel groups of equal sizes (1:1). The study will be conducted double blind. Participants will be randomized into either intervention (IG) or sham control group (SCG), with the study designed to determine the superiority of the effectiveness of the IG compared to the SCG. While each employee of the project can perform recruitment and baseline assessment, the intervention will be carried out exclusively at the Institute for Biomedicine of Aging by trained exercise instructors. The Chair of Health Psychology will be responsible for the outcome assessment, allowing for blinding with regard to group allocation of the participants. All biological specimens will be analyzed by staff at Chair of Health Psychology in the laboratories physically separated from all other project locations. The study complies with the Declaration of Helsinki and Guidelines for Good Clinical Practice. The flow diagram for FEARFALL is shown in Fig. 1.

**Fig. 1 Fig1:**
[figure not shown]
Flow diagram for FEARFALL

## Methods: participants, interventions and outcomes

### Study setting {9}

FEARFALL is a randomized controlled prospective study consisting of parallel groups. In this study, the investigators aim to enroll *n* = 200 community-dwelling older adults, aged 70 years and older, from the Nürnberg/Fürth/Erlangen region (Bavaria, Germany). Eligible participants must exhibit moderate to high levels of CaF, as defined by a score of at least 20 on the 16-item version of the Falls Efficacy Scale-International (FES-I) questionnaire, and possess adequate mobility to travel to the study center.

### Eligibility criteria {10}

FEARFALL’s eligibility criteria are shown in Table 1.

**Table 1 Tab1:** Inclusion and exclusion criteria for FEARFALL study

Inclusion criteria:	Exclusion criteria:
• Age of 70 years or older • FES-I (16-item) score ≥ 20 • Ability to come to the study center without help • Ability and willingness to provide informed consent and accept randomization to either study arm	• Life expectancy of less than 12 months • Participation in another intervention trial (physical exercise or medical) at the same time or within the previous 6 months • Anti-inflammatory drugs (e.g., glucocorticoids, NSAIDs) • Cognitive impairment (Mini-Mental-Status-Examination [MMSE] < 24 points) • Any medical, psychiatric, or behavioral factors that in the judgment of the principal investigator may interfere with the study participation or the ability to follow the intervention

### Who will take informed consent? {26a}

All participants have to provide written consent after reviewing the participant information and engaging in a personal discussion with the trained study staff from IBA to address any remaining questions.

### Additional consent provisions for collection and use of participant data and biological specimens {26b}

For biological specimen, all participants have to sign the informed consent including data retention permission.

## Interventions

### Explanation for the choice of comparators {6b}

The SCG could be seen as standard care, because the participants will receive health lectures and light stretching exercises at the same frequency as the IG. All biological specimen will be collected and analyzed at the same time points in both groups.

### Intervention description {11a}

#### Study procedure

The general study design is that of a randomized controlled trial. After screening and providing written, informed consent, eligible participants will be randomized to participate in either the IG or the SCG of a 16-week intervention period (described in detail below). Randomization will be stratified by gender (female, male, or together as a couple), and statin intake, to ensure equal distribution between both groups. For each group, the intervention or control treatment will be followed by an 8-month follow-up period. This design allows to include 3 data collection time points: T0 at baseline, T1 after intervention or control treatment, T2 at 8 months post intervention. Post-intervention follow-up intervals are selected based on the anticipated trajectories of the development of psychological and psychobiological changes.

### Assessments

All measurements are collected at three time points, T0, T1, and T2, with the exception of demographic variables.

### Demographic variables

At the baseline assessment, general information including demographic information, age, gender, education level, income, current living circumstances, and family status will be collected.

### Biomedical, anthropometric and functional health variables

#### Health status

The health status will be recorded by questionnaire determining the number of diseases and medications.

#### Recent fall experiences

Whether participants have experienced fall events in the 12 months prior to enrollment will be assessed by a standardized questionnaire used in all our previous studies. If a fall has taken place, information about the severity of injuries will be obtained via questionnaire [33].

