### Criteria for discontinuing or modifying allocated interventions {11b}

Criteria for discontinuing the intervention for a participant is an adverse event such as a fall or accident resulting in severe injuries (e.g., fractures), which permanently prevents their participation in the intervention.

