### Outcomes {12}

As the primary outcome, the decrease in CaF after intervention (T1) measured by FES-I score in comparison to the SCG will be confirmed. All secondary outcome measures will be assessed at three time points (T0, T1, and T2) and changes between groups over time will be explored. Therefore, sarcopenia will be assessed by BIA, physical function will be tested by SPPB, and handgrip strength and physical activity will be tested by actigraphy. The VAS scale of EQ-5D will determine health-related quality of life. General psychological status will be explored with questionnaires for depression (GDS), perceived stress (PSS), and anxiety (GAS). Furthermore, MMSE and TMT A and B will determine cognitive function.

Pathophysiological parameters changes will be explored in blood samples such as levels of CRP, IL-6, TNF-alpha, and IL-10 for systemic inflammatory processes as well as gene expression of IL-1beta, IL-6, IL-10, and I-kappa B for intracellular inflammatory activity. In addition, stress system activity will be measured by changes in cortisol and alpha-amylase levels in salivary samples.

If a fall or accident resulting in severe injuries (e.g., fractures) occurs during the intervention period, it poses a potential risk to the participants and is therefore considered an adverse outcome.

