## Data collection and management

### Plans for assessment and collection of outcomes {18a}

Data collection procedure is shown in Table 4. Except of sociodemographic characteristics and cognitive function, all questionnaires and laboratory and functional tests are performed in-person at each visit, respectively. Data collection will be finished in the 2nd quarter of 2025.

After completing data collection for each time point, data entry will be performed contemporaneously to ensure identification of missing data and any discrepancies. This enables to record missing data or incorrect inputs from participants. Prior to hypothesis testing, all data will be cleaned, inspected for outliers, and tested for normality of distribution. Composite scores will be computed were appropriate, e.g., for questionnaires. Laboratory data will be quality checked using standard procedures, including intra- and inter-assay variability. All biomarkers will be analyzed in duplicates, as is done in standard procedures in the laboratory. Laboratory values not complying with quality control requirements will be repeated. Means and standard deviations for all variables will be computed, and preliminary analyses testing for age and gender effects, pre-intervention group differences, and time effects of repeated samples will be performed.

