### Adverse event reporting and harms {22}

Adverse events, e.g., falls and injuries during training, will be recorded.

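### The falls questionnaire is repeated at T1 and T2 but its stated window ends at enrolment, so falls during the trial have no systematic, arm-comparable ascertainment

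*Protocol article*

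**What the plan says.** All references are to the Protocol article.

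- *Recent fall experiences* fixes the recall window: falls "in the 12 months prior to enrollment will be assessed by a standardized questionnaire". If there was a fall, the form also asks how severe the injuries were.
- *Assessments* sets the schedule: "All measurements are collected at three time points, T0, T1, and T2, with the exception of demographic variables". *Plans for assessment and collection of outcomes {18a}* agrees: "Except of sociodemographic characteristics and cognitive function, all questionnaires and laboratory and functional tests are performed in-person at each visit".
- *Study procedure* adds that "the intervention or control treatment will be followed by an 8-month follow-up period".
- *Adverse event reporting and harms {22}* reads: "Adverse events, e.g., falls and injuries during training, will be recorded".
- *Outcomes {12}* names one further category as an adverse outcome: "If a fall or accident resulting in severe injuries (e.g., fractures) occurs during the intervention period". Falls are not among the primary or secondary outcomes.
- *Criteria for discontinuing or modifying allocated interventions {11b}* mentions falls only as "an adverse event such as a fall or accident resulting in severe injuries (e.g., fractures), which permanently prevents their participation in the intervention".
- *Data management {19}* gives a general route. Study coordinators and doctoral students report adverse events to the responsible principal investigator, who informs the supervising bodies within 1 week. There is also a monthly data safety meeting.

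**The concern.** Two stated rules do not fit together. One repeats the falls questionnaire at T1 and T2. The other ties its window to a date that does not move, the date of enrolment. A team that follows both would ask three times about the same year and never about the time on trial.

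This matters because of what the programme does. According to *Objectives {7}* it aims to lower concerns about falling and raise activity. The training also works against avoidance in daily life, progresses balance tasks to no hand support, and includes unsupervised home sessions. Participants are at least 70 years old with an FES-I score of at least 20. More activity could mean more falls, and better balance could mean fewer. A reader of a positive FES-I result will want to know whether lower concern came with more falls in one arm. That needs the same question put to both arms over the same period.

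**Working it through.** **Step 1. Length of the period.** The programme lasts 16 weeks = 112 days. At 365/12 = 30.4 days per month this is 112/30.4 = 3.7 months. With the 8-month follow-up, T0 to T2 is 3.7 + 8 = 11.7 months. The stated window runs from 12 months before enrolment up to enrolment, so its overlap with these 11.7 months is zero, however often the form is given.

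**Step 2. Which falls have a stated route.**

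| Fall | Year before enrolment | 16-week programme | 8-month follow-up |
|---|---|---|---|
| In a training session | not applicable | named example of an adverse event | no sessions |
| Daily life, severe injury | questionnaire | named adverse outcome | general adverse-event route only |
| Daily life, no severe injury | questionnaire | general adverse-event route only | general adverse-event route only |

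The general route says who passes a report on. It does not say how staff learn of a fall at home. No diary, calendar or fall count is described. After T1 the article describes reminder calls and appointment invitations, and for the control arm cards and a social event, but none of these as an occasion to ask about falls.

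**Step 3. A more generous reading.** Suppose staff ask about the 12 months before each visit.

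- At T1 the window would hold 3.7 months after enrolment and 12 − 3.7 = 8.3 months before it, so only 3.7/12 = 31% would be time on trial.
- At T2 it would hold the 11.7 months on trial plus about 0.3 months before enrolment, and it would count again any programme-period falls already given at T1.

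Asked this way, T2 would capture most of what is needed, but T1 would mix baseline and trial falls. The window must therefore be stated even on this reading.

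**Step 4. Could falls be a formal efficacy test?** The documents give no fall rate, so these inputs are assumptions: 20–40% of controls fall at least once, and the risk ratio is 0.7, 0.8, 1.25 or 1.4. *Sample size {14}* gives 200 randomised, 100 per arm, with 25–30% drop-out. That leaves 200 × 0.75 = 150 (75 per arm) or 200 × 0.70 = 140 (70 per arm).

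Power at two-sided 5% = Φ[(|p1 − p2| − 1.96·SE0)/SE1], with SE0 = √(2p̄(1 − p̄)/n) and SE1 = √((p1(1 − p1) + p2(1 − p2))/n).

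- Lowest, 20% v 16%, n = 70: SE0 = 0.0649, SE1 = 0.0649, power = Φ[(0.04 − 0.1273)/0.0649] = 9%.
- Highest, 40% v 56%, n = 75: SE0 = 0.0816, SE1 = 0.0805, power = Φ[(0.16 − 0.1599)/0.0805] = 50%.
- With 100 per arm the same two cases give 11% and 62%.

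Complete counts would therefore support a safety description, not a firm test.

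**The case against.** The case on the other side has four parts.

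1. *The literal reading is strained.* Nobody would sensibly ask about the same pre-enrolment year three times, so the section probably describes the baseline use of a recall form. This may well be what was meant. It does not tell staff which window to use at T1 and T2, and Step 3 shows that the choice matters.
2. *The schedule table is not shown, and an article condenses the full protocol.* The table could show when the form is given. It would not alter the window that the text states. The point rests on two statements in the article that conflict, not on something left out.
3. *Adverse-event capture is wider than training.* This stands. A reader might infer that only falls in sessions are recorded. The harms section gives those falls as an example, the outcomes section covers severe-injury falls throughout the programme, and the data management section has a general route. Both arms also meet equally often, so the chances to report are alike during the 16 weeks. What is missing is a systematic question, above all after T1.
4. *Falls are not an objective.* This stands too. A reader might infer that the trial fails because it cannot show an effect on falls. It does not claim to, and Step 4 shows that it would have little power to do so.

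**Conclusion.** The point holds as an incomplete safety record by arm. As written, the repeated questionnaire covers 0 of about 11.7 months on trial. Non-severe falls in daily life, and falls in the 8-month follow-up, depend on general adverse-event reporting with no stated way of finding them. The primary FES-I comparison is not touched. This is a cheap improvement rather than a flaw in the main result.

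The number of falls missed cannot be given. A reader might multiply an assumed 20–40% of fallers by the 140–150 participants followed (20% of 140 = 28; 40% of 150 = 60) and call these people uncounted. The documents do not support that: they give no fall rate, some of these falls would reach the adverse-event route, and the form may in practice be asked with a later window.

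The conclusion assumes only that the stated window and the stated repeat schedule are both followed.

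**What to change.** Reconcile *Recent fall experiences*, *Assessments*, *Outcomes {12}*, *Plans for assessment and collection of outcomes {18a}* and *Adverse event reporting and harms {22}*:

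- Keep the 12-month window at T0. At all remaining T1 and T2 visits, ask both arms with the same questionnaire about falls and injuries since the previous visit.
- Define falls and injurious falls from T0 to T2 as a safety outcome, reported descriptively by arm and not as a powered test.
- Report them for all randomised participants with data. The handling of non-adherence in {20c} keeps only those with at least 15 sessions, so a person who falls and stops attending could otherwise disappear from the table.

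The cost is a changed recall window on an existing form at existing visits, and one table. There are two downsides. Recall over up to 8 months will undercount minor falls. Data will also be incomplete for early participants: recruitment began in September 2022 and this version is dated 13 March 2024. If T1 follows T0 by 16 weeks, anyone enrolled before about late November 2023 was by then past T1, and anyone enrolled before about late March 2023 was past T2. The report should state how many participants contribute to each period.
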